## Abstract

**Introduction::**

The incidence, mortality, and treatment costs of sepsis are high and, thus, present a major challenge for critical care medicine. Our previous studies suggest that intestinal metabolite granisetron has a potential therapeutic effect on sepsis. Granisetron is a clinically widely used antiemetic, which is safe, inexpensive, and reliable. However, its value in the treatment of sepsis remains unclear. This study aims to explore the efficacy and safety of granisetron in the treatment of sepsis.

**Methods and analysis::**

A single-center, single-blind, randomized, controlled clinical trial will be conducted on 154 patients with sepsis. Patients who meet sepsis 3.0 diagnostic criteria, aged ≥18 and ≤80 years, with PCT ≥ 2 ng/mL will be recruited. Patients will be randomized to receive intravenous granisetron 3 mg every 8 hours (n = 77) or an equal volume of normal saline (n = 77) for a treatment period of 4 days or to ICU discharge. The primary outcome is 28-day all-cause mortality. Secondary outcome measures include requirements for organ function support, changes of organ function, changes in infection biomarkers, changes in inflammatory and immune biomarkers, and the proportion of new organ failure. Adverse events and serious adverse events also will be observed closely.

**Ethics and dissemination::**

The study was approved by the Clinical Ethics Committee of Zhujiang Hospital of Southern Medical University (2018-ZZJHZX-009). The trial results will be disseminated at national and international conferences and through peer-reviewed journal.

**Trial registration::**

NCT03924518.URL: www.clinicaltrials.gov.

**Protocol date::**

1 May 2019. version 2.1.

## Introduction

1

Sepsis is life-threatening organ dysfunction due to a dysregulated host response to infection and has a high mortality rate.^[1,2]^ It is recognized as a primary health threat.^[3]^ Epidemiological studies have shown that 250,000 of the 750,000 patients who suffer from sepsis each year in the United States die as a result of the disease. Treatment costs for sepsis are high. The average cost per patient with sepsis in the United States is $22,000 and about ¥80,000 in China.^[4,5]^ Even for those who survive, the quality of life is significantly worse.^[6]^

At present, the internationally recognized management strategies for patients with sepsis mainly include early active fluid resuscitation, early appropriate antibiotics, hemodynamic support of vasopressin, and identification and control of infection sites.^[7]^ The implementation of the above treatment strategies has caused the prognosis of patients with sepsis to be significantly improved. However, sepsis is a life-threatening organ dysfunction caused by infection. A widespread and uncontrolled immune inflammatory response results in its development and poor prognosis. Although the use of antimicrobials, fluid resuscitation, and organ function support have certainly improved the prognosis, to date, the mortality of sepsis continues to be on the range of 20% to 30%, and in developing countries it is as high as 60%.^[8,9]^ Therefore, it is necessary to find a safe, reliable, and inexpensive new treatment strategy that can reduce mortality further. Recent studies have shown that changes in metabolites produced by gut microbes play a role in the development of sepsis and organ damage. The number of intestinal microbes in normal humans is as high as 10^12^ to 10^14^.^[10]^ The intestinal flora participates in important physiological processes such as nutrient absorption, substance metabolism, and immune defense.^[11]^ Our previous animal studies have confirmed that there is a significant deficiency of intestinal flora metabolites called granisetron in sepsis sensitive mice. This deficiency is closely related to organ dysfunction and death.^[12]^ Administration of granisetron to septic mice has shown to significantly reduce the damage in their liver and lungs, while reducing the mortality rate.^[12,13]^ Subsequently, we also found that in septic patients, fecal granisetron level is negatively related to liver damage.^[12]^ Based on the above findings, we hypothesized that endogenous granisetron deficiency has a significant impact on poor prognosis in patients suffering from sepsis.

Granisetron is a highly selective 5- hydroxytryptamine 3 (5-HT3) receptor antagonist that has been widely used clinically to treat vomiting after chemotherapy with mild side effects, high safety, and low cost.^[14]^ Theoretically, for patients with sepsis, supplementation with granisetron may be an effective treatment for reducing organ damage and improving the survival rate of patients. However, there is no clinical evidence for whether granisetron can greatly improve the prognosis of patients with sepsis than a placebo. We, therefore, designed a study to evaluate the efficacy and safety of granisetron treatment compared with placebo in patients with sepsis.

## Methods

2

The protocol and analysis plan have been reviewed by the Clinical Trial Committee of Zhujiang Hospital (2018LX0003-GY). Patients and the public were not involved in the design of this study. We report our protocol for the GRANTISS trial based on the SPIRIT guidelines.^[15]^

### Design

2.1

The GRANTISS trial is single-center, single-blind, randomized, and placebo-controlled. It is expected to be conducted in the Department of Critical Care Medicine of Zhujiang Hospital from April 23, 2019 to December 31, 2020. The hospital, a large-scale research tertiary hospital in Guangzhou, China, provides treatment mainly to patients from various provinces of South China, covering a wide range; this ensures, to some extent, that the patients recruited are widely representative. The study ends with the last patient follow-up.

Eligible patients will be randomized and placed in the granisetron treatment group or the placebo control group, and all enrolled patients will receive routine standard care and standardized treatment. On this basis, patients in the granisetron-treated group will receive granisetron intravenously, and patients in the placebo-controlled group will receive the same volume of saline.

### Population

2.2

Any patients who are suspected of sepsis or have been confirmed sepsis in intensive care unit (ICU) will be potential candidates. However, we will only include patients meeting the following criteria: age ≥18 years and ≤80 years of age; meet the 2016 International Sepsis Guidelines diagnostic criteria: suspected or confirmed infection and evidence of acute organ dysfunction: for patients without chronic organ dysfunction, sequential organ failure assessment score (SOFA) ≥ 2; for patients with chronic organ dysfunction, SOFA increased by ≥ 2; and procalcitonin (PCT) ≥ 2 ng/mL.

Patients will be excluded if they meet any of the following criteria: age<18 years old or > 80 years; pregnancy or lactation; solid organ or bone marrow transplant; myocardial infarction within the past 3 months; advanced pulmonary fibrosis; cardiopulmonary resuscitation before enrollment; HIV-positive; neutropenia; hematological/lymphatic tumors have no remission; limited care (lack of commitment to full and aggressive support); long-term use of immunosuppressive drugs or immunodeficiency; advanced tumors; combined with noninfectious factors leading to death (uncontrolled large bleeding, cerebral hernia, etc.); persistent infection sources that cannot be removed by puncture and drainage, debridement, or other surgical procedures; allergy to granisetron; intestinal obstruction.

### Screening and informed consent

2.3

Two highly trained screeners will screen for all sepsis patients who meet the criteria. Only patients who have been confirmed by both screeners as meeting the inclusion criteria and who do not meet any of the exclusion criteria will be eligible. If 2 screeners have different opinions on the eligibility of the patients, it will be judged by the principal investigator. After determining that the patient is eligible for inclusion and discussing the risks associated with the treatment with the treating physicians, the screeners need to inform the patients or their families of the purpose of the trial and its risks; then the patients or their relatives must sign the informed consent. For successful enrollment, the screeners should register their enrollment date and basic information in detail. For excluded patients, the screeners should record the reason for the exclusion in detail. During the study period, the primary investigator should conduct a random check on the screening form every month to ensure that all enrolled patients meet the criteria. The screening form will be permanently stored in paper and spreadsheet forms.

### Randomization allocation concealment

2.4

Patients who are eligible for enrollment will be randomized, and they will be assigned with an equal chance to the granisetron and placebo control group, with a 1:1 ratio between the treatment and control groups. The random sequence was generated by an independent Data Security Management Board (DSMB) using Stata 13, and the randomized cards were made by the relevant personnel according to the random sequence. Each random group card was marked with a patient's enrollment group and loaded into a customized sealed envelope. The randomly grouped block lengths will not be made public until the trial is completed. After successful recruitment, the clinical screeners will open the envelope and complete the random assignment based on the randomized information. If more than 1 patient is successfully recruited at the same time, the order of randomization for patients is determined based on the registered time of ICU admission.

### Blinding

2.5

The trial used a single-blind design in which the subjects, subject relatives, and relevant statisticians will remain blind to the trial grouping. To achieve this process, the control group will use normal saline as a placebo with the same appearance as granisetron and use same 50 mL syringes as drug containers and use the word “GRAN” as the drug infusion label.

### Interventions

2.6

The recruited patients will begin the trial intervention within 8 hours after randomization. Patients in the granisetron-treated group will receive granisetron 3 mg (PKU HealthCare Corp, Ltd) diluted to 25 mL with 22 mL of saline and intravenously administered within 10 minutes. Patients in the placebo group will receive 25 mL of normal saline and administer it intravenously within 10 minutes. The trial intervention will be administered at a frequency of 8 hours, with a course of treatment of 4 days or ICU discharge, whatever comes first. Considering the fluctuation of vital signs such as body temperature and blood pressure at different time points in 1 day, to avoid the influence of the abovementioned confounding factors on the trial results, it is stipulated that the trial intervention for each patient will be held at 12:00, 20:00, and 04:00. In addition to the trial intervention, patients will receive routine standard care and routine sepsis treatment according to the 2016 International Management Guidelines for Sepsis,^[7]^ including but not limited to the use of antibiotics, venous fluid resuscitation, use of blood products, enteral or parenteral nutrition, prevention of deep vein thrombosis, and supportive treatment for organ dysfunction. All treatments except study interventions will be determined by the treating physician and will be noted in detail in patients’ medical records.

For patients who may require using antiemetics, any antiemetics that act on 5-HT receptors should be avoided, but other classes of antiemetics such as metoclopramide may be used. Additionally, in the treatment of patients with sepsis, some liver-protective drugs such as reduced glutathione are often used to reduce septic liver damage; because the role of granisetron for liver function protection in clinic is not certain, the use of such drugs to alleviate organ dysfunction by the treating physician will be allowed, but the name, frequency, and dosage of the drug used should be accurately recorded.

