### Data collection

2.7

The patients enrolled in the group will receive clinical or laboratory assessments (Table 1) during the screening period, the drug infusion period, on the first day after the end of trial interventions, and on the 28th day after enrollment. Before treatment (D0; screening period), the following indicators should be evaluated: pathogen culture results, the level of blood 5-HT, acute physiology and chronic health evaluation (APACHE II) scores, and SOFA scores. Before treatment (D0; screening period), on the third day of treatment (D2), and on the first day after treatment (D4), the following indicators will be measured: immune function indicators (white blood cell count, peripheral lymphocyte count, CD4+ and CD8+ T-cell count), renal injury indicators (Cys C), inflammation Indicators (the level of IL-6, CPR, ESR, SOD), and infection indicators (the level of serum PCT, fungi (1,3)-beta-D-Glucan, galactomannan antigen). Daily assessment indicators include the following: liver injury indicators (the level of ALT, AST, total bilirubin, direct bilirubin), the level of blood lactate, renal injury indicators (the level of Cr, BUN), lung injury indicators (oxygenation index, not applicable during extracorporeal membrane oxygenation (ECMO) support), fluid balance, vasoactive drug dose, urine volume, SOFA scores, and concomitant medications that may affect the outcome. Other indicators are the duration of organ function replacement therapy including continuous renal replacement therapy (CRRT), ECMO and mechanical ventilation, the incidence of new dysfunction, ICU stay time, ICU mortality, and 28-day mortality. Safety indicators include adverse reactions and the incidence of serious adverse events. Among them, the 28-day survival information of patients will be obtained by telephone follow-up. For dropout events, the causes will be recorded in detail and these patients will also be followed up. All the laboratory outcomes will be taken from the Central Laboratory of Zhujiang Hospital, and all the indicators needed to calculate the APACHE II score and SOFA score will also be recorded in detail. Furthermore, during the course of treatment, any out-of-plan evaluations of the above indicators by the treating physicians also will be collected. All of the above data will be collected by highly trained clinical observers.

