#### Primary outcome

2.8.1

The primary outcome measure is the all-cause mortality rate at 28 days after enrollment.

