#### Secondary outcome

2.8.2

The secondary outcome indicators mainly include the following aspects:

Requirements for organ function support: the duration of organ function replacement therapy including CRRT, ECMO, and mechanical ventilationImprovement of organ function: the changes in SOFA score; creatinine, transaminase, and cystatin after interventions completion; lactate clearance after interventions completion; and the incidence of new organ dysfunctionImprovements in infection indicators: the changes in PCT after interventions completion, PCT clearance after interventions completion, and changes in fungi (1,3)-beta-D-Glucan and galactomannan antigen after interventions completion.Improvement of inflammatory indicators: the changes in IL-6, ESR, SOD, and CRP after interventions completionImprovement of immune function indicators: the changes in lymphocyte count, white blood cell count, and CD4+ and CD8+ T cell count after interventions completion.The incidence of new organ dysfunction: the incidence of new acute liver injury, kidney injury, and lung injury. New organ failure refers to organ failure that occurs after enrollment.Other indicators: ICU length of stay (LOS).Additionally, we will also collect blood 5-HT levels before and after completion of the treatment to determine if there is a correlation between 5-HT levels and the prognosis of sepsis.

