#### Processing of missing data

2.12.3

Analysis based on modified intent-to-treat population sets using the last observation carried forward method, that is, the case where the entire treatment process is not observed but rather the last observation data is transferred to the final result of the test

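### The post-treatment assessment is fixed both at D4 and at the day after dosing ends; the two disagree for anyone whose dosing stops early, and most marker outcomes follow the second definition

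*Protocol article*

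**What the plan says.** All of this is in the protocol article.

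- **Interventions (2.6):** dosing is every 8 hours, "with a course of treatment of 4 days or ICU discharge, whatever comes first".
- **Data collection (2.7), general schedule:** patients are assessed at screening, during infusion, "on the first day after the end of trial interventions, and on the 28th day after enrollment". The post-treatment visit is tied here to the end of dosing.
- **Data collection (2.7), marker schedule:** immune, inflammatory and infection markers and cystatin C are measured before treatment (D0), "on the third day of treatment (D2), and on the first day after treatment (D4"). The same visit now carries a fixed day number.
- **Secondary outcome (2.8.2):** organ-function outcomes include "creatinine, transaminase, and cystatin after interventions completion; lactate clearance after interventions completion", and infection outcomes include "the changes in PCT after interventions completion, PCT clearance after interventions completion". The fungal, inflammatory and immune markers are defined in the same way, with no study day.
- **Processing of missing data (2.12.3):** incomplete courses are handled "using the last observation carried forward method".
- **Secondary outcome analysis (2.12.9):** quantitative variables are compared by two-sample *t* test, and repeated measures by covariance analysis or a mixed linear model.

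**The concern.** ICU discharge happens after randomisation, and an effective sepsis treatment could bring it forward. If the sampling day follows the end of dosing, it follows that event. PCT, lactate and CRP change over days whatever the treatment, so a value taken on D2 is not comparable with one taken on D4. If granisetron shortened ICU stay, more of its patients would be sampled early, with less time for markers to fall, and a real benefit on those markers would be understated.

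Later analysis may not be able to repair this. Creatinine, transaminases, lactate and SOFA are collected daily, so a fixed-day value can be taken for as long as daily assessment continues. PCT, IL-6, CRP, ESR, SOD, cystatin C, the fungal markers and the cell counts are scheduled only at D0, D2 and the post-treatment visit. If that visit moves, the D4 value of these markers does not exist.

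**Working it through.** **1. Reproduce the protocol's own label.** D0 is the pre-treatment day and the third treatment day is D2, so treatment days run from D0. A full four-day course covers D0 to D3, and the first day after it is D4. The label is therefore right for a complete course.

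**2. Apply the stopping rule.** First day after dosing = last dosing day + 1.

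| Last dosing day | First day after dosing | Days before D4 | Days from D0 |
|---|---|---|---|
| D3 | D4 | 0 | 4 |
| D2 | D3 | 1 | 3 |
| D1 | D2 | 2 | 2 |
| D0 | D1 | 3 | 1 |

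The two definitions agree only in the first row. In the third row the post-treatment sample falls on the scheduled D2 sample, on a day that is no longer a day of treatment. Nothing in the article says which definition governs.

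**3. Illustrate the size on the literal reading.** The documents give neither an early-discharge rate nor a marker slope, so every input here is assumed. Suppose PCT halves daily in both arms, with no drug effect on it.

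- Clearance at day t = 1 − 0.5^t: 0.75 at D2, 0.875 at D3, 0.9375 at D4.
- Arm with 30% sampled at D2: 0.70 × 0.9375 + 0.30 × 0.75 = 0.88125.
- Arm with 20% sampled at D2: 0.80 × 0.9375 + 0.20 × 0.75 = 0.90.
- Spurious difference: 0.90 − 0.88125 = 0.01875, about 1.9 percentage points, against the arm that leaves the ICU sooner.
- On the log2 scale: (0.30 − 0.20) × (4 − 2) = 0.2 units, out of a four-day fall of 4 units (5%).

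**4. Range.** For any constant daily log decline, the spurious difference as a share of the four-day fall is (difference in early shares) × (days early) / 4.

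- 10% against 20%, 1 day early: 0.10 × 1 / 4 = 2.5%.
- 10% against 30%, 2 days early: 0.20 × 2 / 4 = 10%.
- Equal shares and equal timing in both arms: 0.

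**5. With a fixed D4.** Every patient measured has a four-day interval from D0, and under the same assumptions the spurious difference is 0.

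**The case against.** The strongest reply is that the only day number given to this visit is D4, beside a fixed D0 and D2, so the sampling day may already be fixed. The article is condensed and its schedule table is not shown. The missing-data rule also suggests that incomplete courses are regarded as lacking a final value, not as having one taken early. This stands to the extent that a reader who infers that early leavers will definitely be sampled on a floating day goes further than the text. The article supports both readings. What remains is that if D4 governs, the end-of-dosing wording in 2.7 and 2.8.2 is wrong for these patients.

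A second reply is that much is handled already: several organ markers are daily, and a mixed model using assessment time is permitted. That helps the daily markers, but the others have no D4 value to model if the sample is not taken then. The permitted *t* test compares values from different days directly. Carrying the last value forward does not align days either.

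A reader might also infer that early leavers have a shorter window for new organ dysfunction, so that its incidence is roughly halved. The documents do not support this. They state that "New organ failure refers to organ failure that occurs after enrollment", with no link to the end of dosing, and the list of daily assessments gives no end day. Even granting a window of two days instead of four at constant risk, the halving would apply to individual early leavers only. By arm it would be 1 − 0.30 × 0.5 = 0.85 against 1 − 0.20 × 0.5 = 0.90 of full incidence, about 6% in relative terms.

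**Conclusion.** The point holds as a conflict between stated definitions, with a possible bias in secondary marker outcomes on the literal reading. The conflict needs no assumption: it follows from the stopping rule and the two descriptions of the visit.

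The bias requires that end of dosing governs and that early stopping differs between arms in frequency or timing. Its size is unknown. The 1.9 percentage points of PCT clearance, and the 2.5% to 10% of the four-day log fall, rest wholly on assumed discharge shares and slopes. The direction is not assured either: death, or a serious adverse event judged related to the study, also ends dosing early, so recovery is not the only driver.

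The primary outcome is not touched, since "The primary outcome measure is the all-cause mortality rate at 28 days after enrollment". ICU length of stay and duration of organ support are also unaffected. No conclusion about the incidence of new organ dysfunction follows from this point.

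**What to change.** - In 2.7, reconcile the two descriptions by setting the assessment at D4 for every patient alive and in hospital, whether or not dosing has ended or the patient has left the ICU.
- In 2.8.2, replace the end-of-intervention qualifier on the change and clearance outcomes with D4.
- In 2.12.3 and 2.12.9, analyse these markers by actual study day, using the mixed model already allowed. Do not carry an earlier value forward as the final one for patients who die or leave hospital before D4.

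The dosing rule and the sample size of 154 do not change. For early leavers the post-treatment draw is moved, not added. The cost is that some D4 samples must be drawn on the ward and that patients who die or leave hospital before D4 will have no D4 value. The number of such patients in each arm should be reported beside the marker results.
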